**Figure 1 F1:**
[figure not shown]
Overview of the trial procedure.

### Data assessment

Semi-structured interviews and self-report questionnaires will be conducted during the three assessments in this trial. The baseline assessment will take place before randomization and subsequent start of treatment.

For detailed assessment of NSSI, we will use the German version of the SITBI [22]. The SITBI-G is a semi-structured interview to assess the presence, frequency and characteristics of a wide range of self-injurious thoughts and behaviors, including suicidal ideation, suicide plans, suicide gestures, suicide attempts and NSSI [21]. The SITBI-G will be repeated at the post-treatment and follow-up assessment time points.

Furthermore, the baseline assessment comprises a sociodemographic interview, which will gather information about gender, date of birth, state of adolescents’ and parents’ education and current living situation. Comorbid diagnoses will be assessed using the German version of the Mini-International Neuropsychiatric Interview for children and adolescents (M.I.N.I- KID 6.0) [26] and parts of the Structured Clinical Interview for DSM-IV-Axis II (SCID-II) [27]. The M.I.N.I.-KID is a short, structured diagnostic interview for DSM-IV and ICD-10 psychiatric disorders for children and adolescents aged 6 to 17 years. The MINI-KID follows the structure format of the adult version of the interview. The MINI-KID is organized in diagnostic sections, each starting with screening questions for each disorder [26]. All questions are in a yes/no format. The SCID-II consists of a screening questionnaire and a subsequent interview to assess axis II disorders. The questionnaire consists of 117 screening questions for the twelve personality disorders. In the interview only questions answered ‘yes’ require further assessment [27]. In our trial the following parts of the SCID-II interview will be used: avoidant, dependent, borderline and antisocial personality disorder. Traumatic and adverse childhood experiences will be assessed using the German version of the Childhood Experience of Care and Abuse (CECA) interview, which is a semi-structured, retrospective interview [28,29]. The CECA includes detailed assessment of the following types of adversity: loss of a parent, parental neglect and antipathy, physical, sexual and psychological abuse, family arrangements, discord at home, violence between parents, supervision and control of children, role reversal and childhood helplessness. In addition to these adverse experiences, the CECA contains the positive scales: support, closeness to parents, coping and being the parents’ favorite child [28,29]. The sociobiographic history, the M.I.N.I-KID, the CECA and the SCID-II interviews are parts of the baseline assessment and will not be repeated at post-treatment or follow-up.

Three questionnaires need to be completed during the assessment: The German version of the Beck Depression Inventory II (BDI-II) will be used to assess the intensity of depression according to the DSM-IV criteria. It consists of 21 items. Each item is a list of four statements arranged in increasing severity about a particular symptom of depression. The time frame for the response is two weeks. A value of 0 to 3 is assigned for each answer. A total score can be summed up. A score of 0 to 13 indicates minimal depression, 14 to 19 indicates mild depression, 20 to 28 indicates moderate depression and a score 29 to 63 indicates severe depression. A higher total score indicates more severe depressive symptoms. The BDI-II is widely used and is considered reliable (r = .93) and valid (r = .32-68) [23]. The KIDSCREEN questionnaire assesses adolescents’ subjective health and well-being [24]. It is normed for children and adolescent aged between 8 to 18 years. There are three KIDSCREEN instruments available for children and adolescents as well as parent/proxy versions. In our trial we will use the KIDSCREEN-27 which consists of five Rasch-scaled dimensions: physical well-being, psychological well-being, autonomy and parents, peers and social support and school environment. This version is widely used and shows good reliability (α = .70) and validity (r = .56) [24]. The Rosenberg Self-Esteem Scale (SES) is a 10-item self-report measure of global self-esteem. It consists of 10 statements related to overall feelings of self-worth or self-acceptance. The items are answered on a four-point scale ranging from ‘strongly agree’ to ‘strongly disagree’ [25]. The BDI-II, the KIDSCREEN and the SES questionnaires will be repeated at the post-treatment and follow-up assessments.

The *Fragebogen zur Patientenzufriedenheit* (ZUF-8; Patient Satisfaction Questionnaire) is a German questionnaire to assess treatment satisfaction of patients. It consists of eight statements, which are answered on a four-point scale ranging from ‘very satisfied’ to ‘quite dissatisfied’ [30]. The ZUF will be part of the post-treatment and the follow-up assessment.

Table 1 gives a summary of all measures used and the corresponding time of assessment.

**Table 1 T1:** Measures and time of assessment

**Measure**	**Baseline**	**Post-treatment**	**Follow-up**
SITBI-G	X	X	X
M.I.N.I.-Kid	X		
SCID-II	X		
CECA	X		
BDI-II	X	X	X
SES	X	X	X
KIDSCREEN	X	X	X
ZUF-8	X	X	X

*BDI-II* Beck Depression Inventory II, *CECA* Childhood Experience of Care and Abuse interview, *KIDSCREEN* Health Related Quality of Life Questionnaire for Children and Young People, *M.I.N.I- KID* Mini-International Neuropsychiatric Interview for children and adolescents, *SES* Rosenberg Self-Esteem Scale, *SCID-II* Structured Clinical Interview for DSM-IV-Axis II, *SITBI-G* Self-Injurious Thoughts and Behaviors Interview-German, *ZUF-8* Patient Satisfaction Questionnaire.

### Participants’ incentive

All participating adolescents will receive 50 Euro for each of the three assessments.

### Intervention

Each participant will be randomized to one of the two possible treatment conditions (CDP versus TAU). At the end of the trial it is assumed that 40 randomly selected participants will be in each intervention condition.

### Intervention one

Participants will be informed about being allocated to the TAU group via telephone by a trained research psychologist. During this telephone call, they will be encouraged to seek treatment and will be referred to the existing mental health care system. They receive contact details of established child psychotherapists, psychiatrists, clinics or counseling centers. The child psychotherapists, psychiatrists, clinics and counseling center have all been informed about the study and have agreed to take part in it. This collaboration was established to shorten the waiting times (first appointment within 2 to 4 weeks) and to guarantee rapid access to treatment for all adolescents. In addition to the referral, each participant will receive a contact card including the study center's telephone number and the emergency number of our clinic. This card ensures that all participants can contact our psychological staff members if they have any questions or problems at any time, and that participants receive adequate crisis intervention if needed.

### Intervention two

CDP is a manualized, short-term psychotherapy which is designed for 8 to 12 therapeutic sessions. It includes elements of cognitive-behavioral therapy (CBT) and dialectic-behavioral therapy (DBT) and is specifically tailored to the treatment of self-injurious behavior in adolescents. The content of the treatment is structured in a manual for patients and a separate manual for therapists. The modules in the manual were all developed from a comprehensive literature review on the treatment of DSH including associated psychological factors performed by the English authors who originally developed the manual [20]. The program comprises four main modules, which can be individually expanded by optional modules - according to requirements of the patient. The four main modules are promoting therapy motivation and compliance of the subjects, identifying reasons for the existing behavior, testing alternative behaviors instead of NSSI, and stabilizing alternative behaviors to reduce aversive strains, which often activate NSSI. In addition to individual therapy sessions, the participating adolescents will be encouraged to do certain homework, which facilitates preparation and post-processing of the therapy sessions in order to increase their effectiveness. Like the participants in the TAU group, the participants in the CDP will receive a contact card so that they can contact one of our psychological staff members if they have any questions or problems at any time and get access to the clinic's crisis response system.

### Staff

During the trial the study assessments will be performed by a clinical psychologist. It is important to note that data collection and psychotherapy are strictly separated in this trial. The assessments will always be performed by the same clinical psychologist, who is blinded to the randomization and the respective treatment group. The psychotherapists giving treatments are kept unaware of the results of the psychometric assessments.

### Training and support of the staff members

All treating psychotherapists in the CDP will be supervised on a monthly basis by a specifically trained supervisor (with a clinical background in CBT and DBT) who will ensure quality and adherence to the treatment manual. To guarantee good adherence, the therapist documents all sessions in according protocols and, if the participants have agreed, records the session. The protocols are checked every week. In emergency situations, all clients have unlimited access to the on-call system of the Clinic of Child and Adolescent Psychiatry.

### Sample size

With an expected response rate of 25% in TAU and 60% in CDP, a sample size of 40 for each group is needed to achieve sufficient power (85%).

### Statistical analysis

To ensure objectivity of the data collection setting the whole process has been standardized. Data collection and treatment will be strictly separated and performed by different personnel (blinded). The data collection process comprises the baseline, the post-treatment and the follow-up assessment. All analyses will be intent-to-treat analyses. If post-treatment or follow-up assessments are missing, the missing assessment will be filled with the last non-missing value. NSSI, which is the main outcome of this trial, will be assessed using the SITBI-G. A clinically significant improvement is defined as a reduction in the frequency of NSSI by 50%. In this process the TAU group and the CDP group will be compared with each other to determine any differences in primary and secondary outcomes by using a *χ*^2^ - test. As a secondary measure, ANCOVA with group as factor and frequency of NSSI at baseline as covariate will be assessed. Explorative analysis will be executed to account for the influence of childhood trauma, psychiatric diagnosis and personality traits and other factors potentially influencing the patients (for example, gender). Descriptive analysis will be used to characterize the study sample. For nominal data frequencies will be determined, and for continuous data means and standard deviations with confidence intervals will be calculated. A significance level of α = .05 will be chosen. Statistical analysis will be performed using Stata 13.

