### Objectives

The aim of the study is to determine the effectiveness of the German CDP for treatment of NSSI in adolescents as compared to TAU. The main outcome objective of the trial is a clinically significant reduction (or remission) by at least 50% in the frequency of NSSI assessed by the Self-Injurious Thoughts and Behaviors Interview-German (SITBI-G) [21,22]. Secondary outcome criteria are a reduction in symptoms of depression as measured by the Beck Depression Inventory (BDI-II) [23] and an increase in self-reported well-being and self-esteem as measured by the KIDSCREEN [24] and Self-Esteem Scale (SES) [25], respectively. Additionally, comorbid psychiatric disorders and childhood adversity will be evaluated as predictors of therapeutic outcome.

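### A chi-square test is named for secondary outcomes that are scale scores, with no categories or responder rule defined for them

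*Protocol article*

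**What the plan says.** The Statistical analysis section of the protocol article covers both sets of outcomes with one test: the groups are "compared with each other to determine any differences in primary and secondary outcomes by using a" chi-square test. Just before that it gives the only responder rule in the article: "A clinically significant improvement is defined as a reduction in the frequency of NSSI by 50" per cent.

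The Objectives section defines the secondary outcomes by direction of change on instruments. On depression: "Secondary outcome criteria are a reduction in symptoms of depression as measured by the Beck Depression Inventory (BDI-II"). On the other two: "an increase in self-reported well-being and self-esteem as measured by the KIDSCREEN [24] and Self-Esteem Scale (SES").

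The Data assessment section describes these instruments as scales. For the BDI-II, 21 items are each scored 0 to 3, and "A total score can be summed up"; "A higher total score indicates more severe depressive symptoms". Severity bands follow, beginning "A score of 0 to 13 indicates minimal depression, 14 to 19 indicates mild depression". The KIDSCREEN-27 gives five Rasch-scaled dimensions, and the SES is a 10-item scale. Table 1 schedules all three at baseline, post-treatment and follow-up.

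One model for continuous data is named, as a secondary measure: "ANCOVA with group as factor and frequency of NSSI at baseline as covariate will be assessed". Its dependent variable is not stated.

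**The concern.** A chi-square test compares counts in categories. The 50% rule creates categories for NSSI frequency, but nothing in the article does so for depression, well-being or self-esteem. Applying the stated test would mean categorising up to seven scores (one BDI-II total, five KIDSCREEN-27 dimensions, one SES score), with no cut-off named as an endpoint.

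Three things are at stake. Cut-offs chosen later can be influenced by the data. Categorising discards information and so costs power in a trial of only 40 per arm. And the result would be a difference in proportions, whereas the Objectives speak of reductions and increases on the scales, for which a difference in means is the natural summary.

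This is not detail that a condensed article leaves to a fuller document. The article names a test and assigns it to these outcomes.

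**Working it through.** **1. The plan's own figure.** The Sample size section gives response rates of 25% (TAU) and 60% (CDP), 40 per group and 85% power. Alpha is 0.05 (Statistical analysis); two-sided is assumed. The two-proportion formula uses the mean proportion 0.425:

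n = [1.96·√(2·0.425·0.575) + 1.036·√(0.25·0.75 + 0.60·0.40)]² / 0.35² = (1.370 + 0.678)² / 0.1225 ≈ 34.2, so 35 per group.

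With the continuity correction, n = (34.2/4)·[1 + √(1 + 4/(34.2·0.35))]² ≈ 39.7, so **40 per group**. Continuity-corrected power at 40 is 85.3%. The plan's figure reproduces, and the test fits the binary primary outcome. No stated figure covers the secondary outcomes.

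**2. Outcome type against test.**

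| Outcome | Form in the article | Categories set as an endpoint? |
|---|---|---|
| NSSI frequency | 50% reduction, yes or no | Yes |
| BDI-II | Summed total, 0 to 63 | No; severity bands only describe the instrument |
| KIDSCREEN-27 | Five Rasch-scaled dimensions | No |
| SES | 10-item scale | No |

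**3. Illustration of the cost.** The article gives no SD or target difference for these scores. The standardised difference d, the median split and the baseline correlation r below are therefore all assumptions. There are 40 per arm, two-sided 0.05, and normal approximations are used.

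- *Median split, chi-square, d = 0.5.* The proportions above the common median are Φ(0.25) = 0.599 and Φ(−0.25) = 0.401, a difference of 0.197. The null SE is √(0.25·2/40) = 0.1118 and the alternative SE is √(2·0.599·0.401/40) = 0.1096. Power = Φ[(0.197 − 1.96·0.1118)/0.1096] = Φ(−0.20) = **42.1%**.
- *Comparison of means.* Power = Φ(0.5/√(2/40) − 1.96) = Φ(2.236 − 1.96) = **60.9%**.
- *ANCOVA on the scale's own baseline.* Power = Φ(2.236/√(1 − r²) − 1.96). At r = 0.5 this is Φ(2.582 − 1.96) = **73.3%**. At r = 0.6 it is Φ(2.795 − 1.96) = **79.8%**.

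Over a range of d:

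| d | Median split | Means | Loss (points) | ANCOVA, r = 0.5 |
|---|---|---|---|---|
| 0.30 | 18.4% | 26.8% | 8.4 | 34.1% |
| 0.50 | 42.1% | 60.9% | 18.8 | 73.3% |
| 0.65 | 62.9% | 82.8% | 19.9 | 91.9% |
| 0.80 | 80.6% | 94.7% | 14.1 | 98.5% |

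The like-for-like loss from dichotomising is 60.9 − 42.1 = 18.8 points at d = 0.5. The further 12.4 points (73.3 − 60.9) to 18.9 points (79.8 − 60.9) come from baseline adjustment, which is a separate gain.

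**The case against.** The strongest defence is that this is a drafting slip: one test written for all outcomes in a condensed article. The same section plans means, standard deviations and confidence intervals for continuous data, which suggests the scores are regarded as continuous. That is plausible as to intent. But those summaries serve to describe the sample, give no between-group contrast, and leave the stated test as it is.

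A reader might infer that the secondary objectives cannot be analysed at all. The documents do not support that. A chi-square test on the four printed BDI-II bands is feasible and needs no new cut-off. However, the article does not link the bands to the analysis, comparing bands between groups is not the same as estimating a reduction in score, and no bands are given for KIDSCREEN or SES.

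A reader might also infer that the ANCOVA uses the wrong covariate for the scores. Its dependent variable is not named, and with baseline NSSI frequency as covariate it reads most naturally as a supporting analysis of NSSI frequency, where that covariate is right. It is not evidence of a wrong covariate for the scales; equally, it does not supply an analysis for them.

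Finally, it is tempting to quote the whole gap between 42% and 73% to 80% as the cost of the chi-square test. That mixes two effects. Only about 19 points come from dichotomising.

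**Conclusion.** The point stands, limited to the secondary outcomes. The article assigns a categorical test to scale scores for which it defines no categorical endpoint. Taken literally, the analysis would be incompletely specified and inefficient, and it would give no mean difference between groups.

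Under the assumed median split, the loss against a plain comparison of means is about 8 to 20 percentage points of power for standardised differences of 0.30 to 0.80, and about 19 points at 0.5. These sizes are illustrative, since the documents give no effect size, SD or correlation for the scales.

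The primary hypothesis, its chi-square test and the sample size of 40 per group are sound on this point. The sentence should be corrected, but the fault does not threaten the trial's main conclusion.

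**What to change.** Restrict the chi-square test to the 50%-reduction NSSI responder outcome. State that BDI-II, KIDSCREEN and SES will be analysed as continuous scores by ANCOVA, or an equivalent mixed model, with group and that scale's own baseline score, reporting the adjusted mean difference with a 95% CI. Name NSSI frequency as the dependent variable of the existing ANCOVA, if that is what is meant.

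The cost is a change of wording. No new data collection is needed, because Table 1 already schedules each scale at baseline and at both later assessments. The Trial status section reports 22 participants randomised of the 80 planned, so most of the data were still to come and the correction could be made before the outcomes are analysed.

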### Ethical issues

The study will be performed in accordance with the Declaration of Helsinki. Approval for the study was obtained from the ethics commission of the Faculty of Medicine at the University of Heidelberg (Ethics Committee No.: S-363/2011). Only those who have provided written informed consent will be included in the trial. If the participants are younger than 16, caregivers’ written consent must be provided as well. Each potential participant and his/her family will be contacted by telephone and provided with a copy of the information sheets, which include a contact number, so that they have the opportunity to ask questions.

## Discussion

This present study in adolescents with NSSI is the first RCT worldwide that uses the CDP. We are testing the brief therapeutic intervention program to help adolescents who show repetitive NSSI, some of whom have not received any treatment for years. The aim of this treatment program is to end, or at least significantly reduce NSSI. The use of a short-term psychotherapeutic intervention may have many more benefits for these adolescents and their families. For example, adolescents may learn how to better handle their feelings and acquire strategies for a less stressful everyday life, especially with regard to family life.

The potential benefit of the ‘The Cutting-Down Programme’ has recently been shown in the study published by Taylor *et al*. [20]. This study found significant reductions in self-harming behavior, depression symptoms and trait anxiety; however, no control group was used to account for non-specific study effects [20].

In Germany this is the first trial to test a short-term therapy in adolescents engaging in NSSI. It is very important to note that this short-term therapy constitutes a very specific approach with a low threshold because of its short time frame. That should help to increase motivation to access therapy and decrease the fear of being stigmatized or stigmatizing themselves.

To the best of our knowledge, no other such specific treatment for treating young people with NSSI exists worldwide, although prevalence of NSSI is high and has continued to rise within the last year [31]. Most of the approaches for treating NSSI are part of the DBT-A program, which has been primarily designed for patients with BPD and for which evidence for use in adolescents is lacking. However, treating all adolescents engaging in NSSI with a BPD-specific program may not be the best approach, considering financial resources available in many public mental health systems. It is known that the existing programs do not always stop or reduce NSSI. Moreover, many of the adolescents engaging in NSSI do not fulfill the criteria of any psychiatric diagnosis [31]; therefore, a specific program and diagnosis is needed for NSSI itself. In our opinion this new approach may be a better way to encourage young people with NSSI to get necessary and specific treatment, which may be sufficient for termination of NSSI within a short period of time. We propose that the program is very effective in terms of reducing or terminating NSSI and it will not involve high economic costs, especially because it is a short-term program.

### Limitations

The Heidelberg region is a particularly wealthy part of Germany, which may have the effect that our findings cannot be generalized to more rural or socioeconomically poorer areas. However, we aim to include every interested adolescent who fits the inclusion criteria without any regard for background (for example, adolescents who live in assisted living, a children’s home or a more rural region around Heidelberg).

If the program proves to be clinically effective, it can be delivered widely across psychologists, psychiatrists and therapists who deal with NSSI in adolescents.

## Trial status

Baseline assessments and subsequent intervention started in November 2012 and so far 22 participants have been randomized. The entire trial is scheduled to be completed by the end of 2014.

